**3.13 Procedure for Data collection**

A team of trained data collectors would carry out data collection at baseline and end-line. The data collection team would be made up of a physician specialist, optometrist, medical laboratory scientists, nurses and trained nutritionist. The behavioural change intervention would be administered by trained community health nurses who would each be responsible for each community. A three day training would be carried out before baseline assessment and a one-day refresher training prior to end-line assessment. Baseline data and end-line data collection is each estimated to take a week at week zero and thirteen respectively. The data collection team would visit households and administer household questionnaires as well as individual child questionnaires after completing consent and assent procedures. Clinical examinations would be carried out by the physician specialist, the optometrist carry and ophthalmic nurses carry out the eye examination.

A trained phlebotomist would carry out the bloodletting. The nutrition team would carry out the anthropometric assessment, dietary recall and quantification of dietary content of iron, folate, enhancers and inhibitors of iron absorption. Five millilitres of blood samples would be taken for haematological and biochemical analysis. The trained community health nurses would carry out the behavioural change communication intervention at week one, four and eight of the intervention period. Administration of pre-packaged and labelled iron and folic acid syrups would be administered by the community health nurses.

The community health nurses would not be involved in the data collection. The independent data collection team would be blinded to the household randomisation. Other information to be collected would include household characteristics, medication history, details about intake of IFA supplements, adverse events of intervention, out of pocket expenses for adhering to interventions, morbidity and mortality outcomes.

**3.14 Project Management**

***3.14.1 Reconnaissance visit***

A team led by the PI will conduct a reconnaissance visit to the six targeted communities. This visit will afford the team a good understanding of the project communities. This will also give the PI the opportunity to improve the proposed sampling and field strategies, as well as establish critical contacts with key stakeholders in the project communities.

***3.14.2 Development of Field Management Plan, Training Plans and Manuals***

Based on the outcomes of information obtained from the reconnaissance survey, the study will develop Data Collection Management Plan – which will include deployment of staff, data collection process and supervision plans. This plan will further be broken down into instructional materials for both supervisors and interviewers on the project. In addition, a Training Plan and Manual to guide the training of enumerators would be prepared. Questionnaires will be programmed onto a computer-based platform to allow for data collection using tablets or phones. The tablets will be used in the training of enumerators and pre-testing of quantitative tools.

***3.14.3 Recruitment of Interviewers***

About Ten enumerators/ field staff would be selected for the training (Eight will be selected for the study). The basic criterion for the recruitment of these individuals are a minimum of a Higher Diploma or University Degree in Nursing, Nutrition, and Medical Laboratory sciences or related fields. Other criteria would include experience in similar assignments, experienced in conduct of participatory research, and mastery of widely spoken local languages within the targeted district.

***3.14.4 Training of Field Staff and Pre-testing***

Based on the Training Plan, a centralized training will be organised to ensure standardisation of delivery and understanding by field staff. The training programme will be scheduled over a period of 5 days (inclusive of a 1 day for pre-testing). A joint session will be organised for all participants on the first day of training, after which they would be trained in their respective teams. This session will focus on general issues as follows:

- General issues including the project background, data collection plan and deliverables, research ethics, quality assurance procedures among others.
- Understanding of the questionnaires and guides
- Administration of Quantitative Questionnaires
- Attitudes and behaviours for field data collection among others

Training on the second and third days will be administered in three groups, namely,

1. Quantitative Class, which will consist of quantitative enumerators
2. Laboratory and phlebotomy class
3. Nursing/ follow-up class

In the group sessions, the training will focus on the data collection and study protocols

***3.14.5 Pre-testing of Tools and Skills***

Following three (3) days of classroom training, the field teams will be sent to one of the communities in the District, however not sampled to test their understanding and skills for the survey, and adequacy of the tools. On the fifth day, the teams will reconvene at the training centre to discuss the findings and field issues.

***3.14.6 Mobilisation of Logistics and Equipment***

The study will also use the time to mobilise logistics in preparation for the training and implementation of the field work. As a minimum, the following provisions will be made for the study; a 4x4 cross country vehicle, laptops, Mobile Tablets (for quantitative teams), external hard drive and pen drive, printed copies of questionnaire and guidelines, notepads and pens, name tags and introductory letters among others.

***3.14.7 Finalisation of tools and Upload on Survey Platform,***

The synthesized feedback will be used to update the tools for study. Once data feedbacks are used to update the quantitative tools (Household and Structure Observation Checklist) questionnaires will be uploaded to the survey platform and then downloaded to the mobile tablets.

**3.15 Description of study tools**

An electronic data collection system would be used in this study. Anthropometric measurement would be carried out using an electronic scale, stadiometer or infantometer depending on the age of the study participant, a shakier tape would be used to measure Mid Upper-Arm Circumference. A non-elastic tape measure would be used for other anthropometric measurements such as head circumference and abdominal circumference.

***3.15.1 Electronic data collection tool***

Data would be captured using an android seven-inch tablets with application programmed to suit the data to be collected. The programme would help in navigating the data collection team through a step-by-step process while interviewing household heads, mothers and making assessment and other measurements on study participants. All required information to be collected at each visit would be highlighted and the data collected guided through each step using a user-friendly interface.

The android application would have some data validation rules to prevent errors during data collection. Some of the rules would include logical and checks on acceptable ranges for each variable. It would also include skipping rules and guidelines and reminders on data that must be collected and entered. All data collection team members would have to log in using a pre-assigned unique server ID and password. Data collectors would be required to enter all required registration information of the child into the system and would be able to access information to which the respective data collector is assigned.

During the subsequent visits, the application would provide each data collector the list of children and households on which follow-up is required. The application would use a geographical information system data collected at the point of follow-up to verify physical presence at the data collection point. Stored data on the local android device would be uploaded to a central server. A backup copy of the database would be stored on a different server and daily updated.

***3.15.2 Questionnaire***

The questionnaires would be available on the android application and the data collector guided to complete the questionnaires. A demographic and household questionnaire would be administered at baseline of the study. Other questionnaires include a household questionnaire, and individual questionnaire for all children participating which would be completed by the primary care-giver or mother.

**3.16 Development of Locally available Dietary intervention for behavioural change communication**

The Locally available dietary intervention to be developed would be adapted from the WHO guide for dietary diversification and enhancing bioavailability of absorbed micronutrients. The guide has five points which would be locally adapted and include locally available food examples. The locally available foods would be selected with expect consultation and use of food composition table.

**Table 3.2** **WHO guide for food diversification and enhancing bioavailability of absorbed micronutrients**

| **WHO guide for food diversification and enhancing bioavailability of absorbed micronutrients** |
| --- |
| - Increase the production and consumption of iron-rich foods, primarily animal-source foods such as meat (especially red meat), poultry and fish, but also iron-rich plant sources such as legumes. - Increase the production and consumption of foods that are rich in vitamin A/carotenoid, such as green leafy vegetables, orange-fleshed fruits and vegetables (e.g. orange-fleshed sweet potatoes), dairy products, eggs, liver and fish oils. - Add fruits and vegetables that are rich in citric or ascorbic acid (e.g. citrus fruits) to the diet, to increase the absorption of non-haem iron. Vitamin C degrades with cooking, so consumption of uncooked (or lightly cooked) fruits and vegetables with high vitamin C content should be encouraged (assuming considerations of food hygiene and food safety are addressed). - Identify and promote culturally appropriate and feasible methods of food processing and preparation, to improve bioavailability and absorption.   *Iron*: germination, fermentation and soaking may improve absorption.  *Vitamin A*: short cooking times and steaming rather than boiling will maintain pro-vitamin A activity.   - Avoid combining known inhibitors of iron absorption with meals that are high in iron content; for example: separate tea and coffee drinking from meal times; consumption 1–2 hours later will not inhibit iron absorption; consume dairy products (milk, cheese and other foods made from milk) as a between meal snack, not at a meal time |

**3.17 Ethical consideration**

Written informed consent would be sought at the cluster level from the head of the household. Verbal assent would be obtained from individual study participant. The consent would be obtained at the baseline before randomisation into the study arms. The proposal would be submitted to the Ghana Health Service ethical review board and the Tamale Teaching hospital institutional review board for review. This trial would be registered with the appropriate clinical trial registry.

Some of the ethical considerations that will be strictly adhered to are as follows;

- All participants would receive the iron folic acid interventions
- Children randomized into no locally available dietary intervention groups would receive the LAD intervention at the end of the study.

The study will:

- ensure appropriate, safe, non-discriminatory participation of all stakeholders.
- promise to pay special attention to the needs of children and other vulnerable groups. Field Staff will be oriented on gender and child right issues as a critical consideration for the data collection exercise.
- respect the confidentiality and anonymity of the response from participants. And all field staff will be trained and supervised accordingly.
- solicit the informed consent of all respondents during the data collection phase through filling of Informed Consent Forms that clearly explains the purpose and the benefits of the study. All participants will be made to participate in this survey voluntarily.
- adopt a community entry procedure suitable to the traditional and cultural practices of the project communities.

**3.18 Data Collection and Monitoring of Field Work**

Data collection will be guided by the data collection management plan and quality control strategies. Once data collection tools are finalised, the study team will mobilise in readiness for the fieldwork and general data collection.

The field level quality control strategy will be defined and articulated in a field manual providing guidance to all field staff during data collection. This will include guidelines about how to engage respondents, the communication channels during fieldwork and ethical standards for data collection.

On the field, the Field Coordinator will meet the enumerators at the end of each day to summarize and evaluate data collected, identify gaps and define ways to fill them. As indicated earlier, the study will adopt electronic data collection system (Kobo or ODK Collect) for the questionnaire using Tablets. Data will on daily basis be downloaded for review and cleaning.

**3.19 Data Cleaning and Editing**

With the mobile based data collection, data is sent regularly (at least daily) to a server and from the server downloaded in a format (exportable to STATA) and scanned for any errors. On an on-going basis, the PI will support the quantitative enumerators to clean the data. A four-stage process will be adopted for ensuring the quality of the quantitative data, as follows:

- *Each Quantitative Interviewer would be required to edit and check for errors on all surveys conducted before submitting the tablets to the PI.*
- *It would be compulsory for the PI to scrutinise the Surveys on the Tablets before submitting the day’s work onto the server.*
- *The PI (who has the overall responsibility of quality assurance) will download the data and scan for errors before approving the next schedule for the team.*
- *At the end of the study, the PI and data collection team will do a final review before the data is analysed.*

*S***3.20 Data Analysis**

Data analysis would be by intention to treat and per protocol basis. Descriptive statistics would be used to describe and display a baseline characteristics of study participants by study arms to allow for comparing of the study arm after randomisation. The primary outcomes are the change in mean haemoglobin concentration and change in proportion of iron deficiency calculated from serum iron results for each arm of the study. This would be obtained by computing the mean change in haemoglobin concentration of each study participant within the study arm. A two-sample Student’s t-test assuming equal variances would be performed to test the hypothesis that the resulting mean haemoglobin from the two arms of the study are equal. Change in proportion of anaemic (ie, haemoglobin concentration <110 g/L), severely anaemic (ie, haemoglobin concentration <70 g/L) would be obtained for all groups. Nutritional z scores will be calculated according to the WHO growth reference curves with the use of Epi Info version 7.2.2.2. Weight-for-height, height-for-age, and weight-for-age z scores of less than −2 would be classified as wasting, stunting, and underweight, respectively; z scores of less than −3 would be considered to indicate severe wasting, severe stunting, or severe underweight. Underweight (ie, weight-for-age Z scores less than −2), and wasted (ie, weight-for-height Z scores less than −2); mean prevalence of diarrhoea, dysentery, and acute respiratory infection based on 7-day maternal recall and cumulative mortality would be analysed.

The trial is designed with the sample size and power considerations to detect a 0·2 difference in length-for-age, height for weight Z scores, a reduction of 8 percentage points in stunting, and a 2·6 g/L shift in haemoglobin for the marginal effect of either intervention, with 90% power and type 1 error of 5%. Selected covariates would be entered in a multivariable regression model; a forward stepwise selection procedure would be implemented with p<0·2 to enter. A log-binomial specification would be used to facilitate estimation of Risk Ratios (RR).

Depending on the analysis, other methods for comparison of groups while accounting for within-cluster correlation would include multinomial and ordinal regression models with robust variance estimation.

In a per-protocol analysis, the study will examine the effect of the interventions when behaviour change modules were delivered at high fidelity (hereby predefined for the Locally available dietary intervention groups as receiving twelve core modules and for all study groups, receiving all iron folic acid as scheduled with a missed dose rate less done 5%, calculated positive change in weekly dietary audit of intake of promoted locally available dietary intervention.

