**3.2 Study design**

This study will be a community-based cluster randomized, controlled trial, with two parallel arms. Included communities shall be randomly selected. Cluster assignment is at the level of household for the locally available dietary (LAD) intervention. The study would follow the closed cohort of eligible households with children aged between 6 to 56 months at baseline for 12 weeks. All eligible children within the household would be included in the study. The interventions would be administered throughout the 12 consecutive weeks of the study. Primary outcome data would be collected at baseline (pre-intervention) and then at the end of 12 weeks (post intervention). Eligible children within the household are the unit for analysis and the clustering would be taken into account.

Cluster randomization was chosen for practical reasons and also to minimize contamination. Children of the same household eat from the same pot. Since the study assess behavioural change communication targeting intake and avoidance of enhancers and inhibitors of iron absorption, it was more appropriate to randomized at the level of the cluster, instead of individual randomization. LAD intervention would be administered at household cluster level. Households must have at least a child aged 6 – 56 months at baseline.

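### The haemoglobin t-test named in section 3.20 and the abstract reflects neither the household clusters nor the haemoglobin strata used in randomisation, and conflicts with section 3.2

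*Protocol*

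**What the plan says.** Section 3.2 sets the unit of randomisation: "Cluster assignment is at the level of household for the locally available dietary (LAD) intervention". It then sets the unit of analysis and makes a commitment: "Eligible children within the household are the unit for analysis and the clustering would be taken into account". One reason it gives for randomising households is shared diet: "Children of the same household eat from the same pot".

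Section 3.10 adds that households are stratified by mean household haemoglobin and randomised in blocks within strata.

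Section 3.20 works at child level, "computing the mean change in haemoglobin concentration of each study participant within the study arm", and names a two-sample Student's test for the arm comparison: "t-test assuming equal variances would be performed to test the hypothesis that the resulting mean haemoglobin from the two arms". The abstract gives the same test. Neither place mentions a household term or a stratum term.

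Within-cluster correlation appears in section 3.20 only in its closing sentence on supplementary methods, whose use is left conditional on which comparison is being made: "other methods for comparison of groups while accounting for within-cluster correlation would include multinomial and ordinal regression models with robust variance estimation".

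**The concern.** Children in one household share food, carers and exposure to infection, so their haemoglobin responses are likely to be correlated. The dietary intervention itself acts through the shared pot. A t-test on children counts each child as an independent observation. When responses within a household are positively correlated and whole households are randomised, this understates the variance of the arm difference.

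The protocol recognises clustering when it sizes the trial, since section 3.7 uses an ICC and a design effect, but the named test leaves it out. The closing sentence on other methods does not fill the gap: multinomial and ordinal models do not estimate a difference in mean haemoglobin, and they are presented as additions to the t-test. The log-binomial model for risk ratios is also named without a cluster term.

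At stake is the error rate of the test on a primary outcome, and with it the confidence interval that readers will take as the trial's main result.

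**Working it through.** **Inputs from section 3.7.** Mean cluster size m = 1.7 (rounded there to 2); coefficient of variation of cluster size cv = 0.90; ICC = 0.010; design effect 1.03; 54 households and 92 children per arm; two-sided 5% level (the formula uses z at α/2); power 80%; dropout 5%; contamination 10%.

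**Reproducing the plan's figures.** Comparing 82% with 62% (20 percentage points) needs 78 children per arm. Then 78 × 1.03 = 80.3, and 80.3 × 1.15 (5% + 10%) = 92.4, against the stated 92. The design effect for unequal clusters is

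DE = 1 + ((cv² + 1) × m − 1) × ICC.

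With m = 2 this is 1 + (1.81 × 2 − 1) × 0.010 = 1.026, which rounds to the stated 1.03. With m = 1.7 it is 1 + 2.077 × 0.010 = 1.021. The sample size therefore includes an allowance for clustering that the named test omits.

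**Real size of an unadjusted test, clustering only.** Type I error = 2 × (1 − Φ(1.96 / √DE)). The correct confidence interval is √DE times as wide as the one reported.

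At the protocol's ICC: DE 1.021 gives 5.2%, and DE 1.03 gives 5.3% with a correct interval about 1.5% wider.

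The documents give no other ICC. The range below is assumed, with m = 1.7:

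| ICC (assumed) | DE, cv 0.9 | Type I error | Correct CI width | DE, cv 0.5 | Type I error |
|---|---|---|---|---|---|
| 0.1 | 1.208 | 7.5% | ×1.10 | 1.113 | 6.3% |
| 0.3 | 1.623 | 12.4% | ×1.27 | 1.337 | 9.0% |
| 0.5 | 2.038 | 17.0% | ×1.43 | 1.562 | 11.7% |

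A null simulation without stratification used 54 households per arm, sizes 1 + Poisson(0.7) (cv about 0.5) and 10,000 runs. The child-level t-test rejected 4.8%, 5.9%, 8.9% and 12.0% of the time at ICC 0.01, 0.1, 0.3 and 0.5, against 4.6% at ICC 0. A t-test on household means rejected 4.7 to 5.1% throughout.

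**Adding the stratification of section 3.10.** Balancing the arms on household mean haemoglobin reduces the real variability of the arm difference. A t-test that omits the strata does not credit that reduction, so it tends to reject too rarely. Null simulations with randomisation balanced on household mean haemoglobin, and an assumed baseline to end-line correlation of 0.5, gave about 3.4%, 4.0%, 6.7% and 9.4% at ICC 0.01, 0.1, 0.3 and 0.5. The two omissions work in opposite directions, and which one wins depends on quantities the protocol does not give.

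**The case against.** The strongest reply is that, by the protocol's own figures, clustering hardly matters. With fewer than two children per household and an ICC of 0.010, the error rate moves from 5% to about 5.2 or 5.3%. That stands.

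The larger error rates need assumed ICCs, and there are reasons to expect them to be moderated:

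- Section 3.20 computes change per child, and differencing removes stable household components.
- Section 3.5.1.2 enrols only children below 11.0 g/dl, which narrows the range of values and makes clusters smaller. If about 68% of under-fives qualify independently (50/60 × 0.82, an assumption), the multiplier 2.077 falls to about 1.42. At cv 0.9, the type I error from clustering is then about 6.7%, 10.1% and 13.4% at ICC 0.1, 0.3 and 0.5.
- The 17% figure combines the highest assumed ICC with cv 0.90.

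A reader might infer that the false-positive rate must exceed 5%, or that a significant result would be invalid. The documents do not support this, because the omitted strata pull the other way and at ICC 0.01 or 0.1 the simulated test was conservative. A reader might also infer that the sponsor refuses to adjust for clustering. Section 3.2 makes a general commitment to adjust, the list of other methods is not worded as exhaustive, and a statistical analysis plan that is not shown may specify a suitable model.

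These points limit the size of the harm and leave its direction open. They do not reconcile the sections: the one test the protocol names for mean haemoglobin, in two places, does not match its design.

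**Conclusion.** The point holds as a mismatch between the stated haemoglobin test and the design. Households are randomised within haemoglobin strata and section 3.2 commits to allowing for clustering, but the named t-test does neither. Its p-value and interval cannot be relied on to have their nominal properties.

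The size is conditional. At the stated ICC of 0.010 the clustering error alone is negligible (about 5.2 to 5.3%). At assumed ICCs of 0.1 to 0.5 with m = 1.7, clustering alone gives about 6 to 17%, depending on cluster-size variation. Omitting the strata offsets this by an amount that depends on the unstated baseline to end-line correlation, so the net direction is not determined. The case for changing the text is that the validity of a primary test should not depend on an ICC given without a source, or on two omissions happening to cancel.

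**What to change.** In section 3.20 and the abstract, replace the t-test with a linear mixed model for haemoglobin with a random intercept for household. Linear regression with household-clustered robust standard errors and a small-sample correction would also serve. Adjust for baseline haemoglobin and the randomisation stratum. Account for household clustering in the anaemia risk ratio as well, report the estimated ICC, and make sections 3.2, 3.20 and the abstract agree.

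The cost is rewording and slightly more analysis work, with no change to data collection or enrolment. If the ICC is near 0.010, little changes on account of clustering. If it is material, confidence intervals may widen: on the clustering arithmetic alone (m = 1.7, cv 0.9), by about 10% at an ICC of 0.1 and 27% at 0.3. Adjustment for baseline haemoglobin and stratum may recover part of that.

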**3.3 Interventions**

Intervention pertains to both cluster and individual level. At the cluster level, randomised household would each received targeted LAD intervention aimed at promoting the intake of locally available iron, folate and vitamin B12 rich foods, food rich in enhancers of iron absorption and discouraging the intake of food rich in inhibitors of iron absorption. The rest of the interventions are targeted at the individual participant level. All study participants would receive the current practiced standard treatment for anaemia; iron + folic acid.

The standard care arm would receive only the iron plus folic acid syrup. The standard plus arm (arm two) would receive iron, folic acid syrup treatment plus LAD intervention. All two arms of the study would run parallel and would be randomized in the ratio 1:1. The dosage of Iron and folic acid to be dispensed would be according to the current WHO recommended dose for age of the child [26].

Each study participant is required to take the prescribed doses daily. Monthly iron and folic acid requirement shall be dispensed to mothers/guardians. A member of the study team shall visit each household every week to monitor the administration of the iron and folic acid. Behavioural change communication administered at household level shall include a set of five points counselling guideline promoting the intake of food rich in enhancers of iron absorption and discouraging the intake of food poor in enhancers iron absorption. This guideline would be administered monthly to randomized households in a LAD arm. In all mothers/guardians of households randomized for LAD would receive three monthly BCC counselling. A monthly semi-quantitative assessment of intake of iron, folic acid and vitamin B12 intake as well as known inhibitors/enhancers of iron absorption of iron intake shall be determined at baseline (week 0), and then weeks 4, 8 and 12.

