**3.7 Sample size calculation**

The sample size was calculated to determine the minimum difference in prevalence of anaemia between arms of the study. The following information was used:

1. Estimated prevalence of anaemia at baseline is 82%, and an estimated 20% reduction after 12 weeks.
2. Estimated average cluster size; which is the average number of children per household is 1.7 (≈2) obtained by the ratio of number of children aged less than five years (7,101) to the number of households in the district (4,133).
3. An estimated intra-cluster correlation (ICC) of 0.010
4. Estimate of coefficient of variation of cluster sizes of 0.90
5. Power of at least 80% (0.80)
6. Significance level of 5% (0.05)
7. Allowing for a cluster randomization design effect of 1.03 and
8. A dropout rate of about 5% for the 12 weeks period,
9. A contamination effect of 10%

With the above considerations, and using a menu driven facility for sample size calculation in cluster randomized controlled trial [71] available as add-on in STATA (version 11.1, StataCorp, Special Edition, College Station, Texas 77845 USA), the minimum sample size and number of cluster per arm was calculated. The computation made use of the following formula for calculating the number of clusters (households) [71]:

$$k=1+\frac{n_{i}}{m}+\mathrm{CVIF}$$

Where

$$\mathrm{CVIF}=\frac{{cv}_{clusters}^{2}\left( \mu_{1}^{2}+ \mu_{2}^{2} \right)\left( z_{\alpha/2}+z_{\beta} \right)^{2}}{d^{2}}$$

And

k = number of clusters required per study arm

$n_{i}$= number of sample size required under individual randomization

*m* = number of clusters required per arm

*d* = pre-specified difference

${cv}_{clusters}$= intra-cluster correlation (ICC) coefficient

$z_{\beta}$ =Maximum available power

$z_{\alpha/2}=$Denotes the upper ${100}_{\alpha/2}$ standard normal centile

$\mu_{1} and \mu_{2}$ = mean/proportion per study arm

The minimum sample size per arm is 92 and the number of clusters per study arm is 54 households (minimum sample size/ average cluster size= 92/1.7). Considering this study proposes two parallel arms, the total minimum study sample size is 184 and the minimum number of households is 108 households.

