**Children (n=)**

**Iron, Folic Acid LAD**

**Allocated intervention**

**Cluster (n=)**

**Children (n=)**

**Did not receive**

**Cluster (n=)**

**Children (n=)**

**Iron, Folic Acid Albendazole LAD**

**Allocated intervention**

**Cluster (n=)**

**Children (n=)**

**Did not receive**

**Cluster (n=)**

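### Section 3.20 claims 90% power for growth, stunting and haemoglobin effects of "either intervention"; this contradicts section 3.7 and the two-arm design, is unreachable for stunting at 92 children per arm, and is unsupported for the other two

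*Protocol*

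**What the plan says.** Section 3.7 (Sample size calculation) bases the size on anaemia prevalence: 82% at baseline with a 20% reduction. It lists "Power of at least 80% (0.80"), a 5% significance level, a design effect of 1.03, 5% dropout and 10% contamination. It arrives at 92 children per arm and concludes that "the total minimum study sample size is 184 and the minimum number of households is 108 households".

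Section 3.20 (Data Analysis) then says the trial was designed "to detect a 0·2 difference in length-for-age, height for weight Z scores", "a reduction of 8 percentage points in stunting" and a 2.6 g/L shift in haemoglobin, "for the marginal effect of either intervention, with 90% power and type 1 error of 5" per cent. None of these three targets appears in 3.7. The protocol gives no SD for haemoglobin or Z scores and no baseline stunting rate.

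On design, section 3.3 (Interventions) says "All two arms of the study would run parallel and would be randomized in the ratio 1:1". Every child receives iron and folic acid, so LAD is the only randomised component. Figure 3.2 in section 3.21 nevertheless lists four groups, two of them with albendazole, including "Iron, Folic Acid Albendazole LAD".

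**The concern.** The protocol carries two power statements for one sample. They differ in power (80% against 90%), in the endpoint that set the size, and in the number of randomised interventions. A marginal effect of either of two interventions belongs to a factorial trial. The four-group flow diagram points the same way and suggests text left over from another design, although the protocol does not say so.

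Mean haemoglobin is a primary outcome (3.12.1) and the one for which 3.20 names a test. The unsupported claim therefore touches the main result as well as the secondary growth outcomes. A reader who relies on 3.20 would credit the trial with a sensitivity that the protocol does not justify.

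**Working it through.** **Inputs from the protocol.** From 3.7: n = 92 per arm, design effect 1.03, dropout 5%, contamination 10%. From 3.20: 0.2 Z, 8 percentage points, 2.6 g/L, 90% power, 5% type 1 error (taken as two-sided).

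**Assumptions, because the protocol gives no figure.** Z-score SD 1.0–1.4, haemoglobin SD 10–14 g/L, base stunting rate 20–50%. Comparisons are unadjusted unless stated.

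**1. Where 92 comes from.** Pooled two-proportion formula, reading the 20% reduction as 82% to 62%, at 80% power:

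n = {[1.96·√(2 × 0.72 × 0.28) + 0.8416·√(0.82 × 0.18 + 0.62 × 0.38)] / 0.20}² = 77.9, so 78.

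78 × 1.03 × 1.15 (5% and 10% added together) = 92.4. Dividing by 0.95 and 0.90 instead gives 94.0. So 92 is consistent with 80% power on anaemia prevalence. Nothing in 3.20 is needed to obtain it.

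**2. Stunting (no SD needed).** With m the mean of the two rates,

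power = Φ{[0.08·√92 − 1.96·√(2m(1 − m))] / √(p₁(1 − p₁) + p₂(1 − p₂))}.

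- 8% to 0%: (0.7673 − 0.5432)/0.2713 = 0.826, power 79.6%. This is the maximum over all base rates (100% to 92% gives the same value).
- 20% to 12%: (0.7673 − 1.0162)/0.5154 = −0.483, power 31.5%.
- 30% to 22%: 23.4%. 40% to 32%: 20.3%. 50% to 42%: 19.1%.

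Ninety per cent would need about 440 per arm from 20% and 814 from 50%.

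**3. Z scores and haemoglobin.** Power = Φ[(δ/SD)·√(n/2) − 1.96], with √(92/2) = 6.782.

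| Target | SD | Power at 92 | Power at about 85 |
|---|---|---|---|
| 0.2 Z | 1.0 | 27% | 26% |
| 0.2 Z | 1.2 | 20% | 19% |
| 0.2 Z | 1.4 | 16% | 15% |
| 2.6 g/L | 10 | 42% | 40% |
| 2.6 g/L | 12 | 31% | 29% |
| 2.6 g/L | 14 | 24% | 23% |

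The last column uses the effective size 92 × 0.95 / 1.03 = 84.9.

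**4. SD that 90% would require at 92 per arm.** SD = δ / [(1.96 + 1.2816)·√(2/92)] = δ / 0.4779. This gives 0.42 for 0.2 Z and 5.4 g/L for 2.6 g/L.

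**5. Effect of baseline adjustment.** With baseline correlation r the residual SD is SD·√(1 − r²). At 92 per arm:

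- r = 0.5: 35% for Z (SD 1.0), 40% for haemoglobin (SD 12).
- r = 0.7: 48% and 54%.
- r = 0.9: 88% and 92%.

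A simple change score has SD·√(2(1 − r)), which is smaller than the end-line SD only when r exceeds 0.5.

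**6. Detectable with 80% power at about 85 per arm.** (1.96 + 0.8416)·√(2/84.9) = 0.430 SD. For haemoglobin this is 4.3 g/L (SD 10) to 6.0 g/L (SD 14). For Z scores it is 0.43 (SD 1.0) to 0.60 (SD 1.4). Both are before the 10% contamination.

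**The case against.** The power percentages for Z scores and haemoglobin rest on SDs that the protocol does not give. A haemoglobin SD of 8 g/L would give 60%. Nor is the unadjusted calculation the most favourable case: 3.20 computes each child's change in haemoglobin and foresees multivariable regression, and growth is measured at weeks 0 and 12. A high baseline correlation could bring both targets close to 90%. This stands, and it is why those two claims are called unsupported and not impossible. It does not rescue the sentence, because the protocol states no correlation or SD that would justify it.

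A reader might infer that none of the three effects could be detected with 90% power under any analysis. The documents support that only for stunting, and there for an unadjusted comparison. A reader might also infer that null results would be reported as proof of no effect. No section sets such a rule.

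It is also fair to say that the sentence drives nothing in the conduct of the trial: the sampling plan uses the 184 children from 3.7 and the intervention budget rounds this to 200. The four-group figure is a consistency matter and adds no evidence about power. Neither point reconciles 3.20 with 3.7.

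**Conclusion.** The point holds in this form. The power statement in 3.20 contradicts 3.7 on power and on the sizing endpoint, and it contradicts the two-arm design on what is randomised. These contradictions need no outside figure. The stunting claim is wrong at 92 per arm for an unadjusted two-sided comparison at any base rate. The Z-score and haemoglobin claims are unsupported. The ranges of 16–27% and 24–42% apply only under the assumed SDs and without adjustment, and they fall slightly after the stated design effect and dropout.

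Naming 3.7 as the basis of the sample size records how it was set and does not endorse its inputs. Section 3.7 assumes 82% anaemia at baseline, whereas 3.5.1.2 enrols only children below 11.0 g/dL, all of whom are anaemic by the definition in 3.6.

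**What to change.** Delete the power sentence in 3.20. In its place:

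- State that the trial was sized in 3.7 on anaemia prevalence at 80% power, and not on growth or mean haemoglobin.
- Give the differences detectable with 80% power at the effective size of about 85 per arm, with the assumed SDs named: haemoglobin about 4.3–6.0 g/L (SD 10–14 g/L) and Z score about 0.43–0.60 (SD 1.0–1.4). Say that these are unadjusted and before contamination. If adjustment is to be credited, state the assumed baseline correlation and its source.
- Refer only to the effect of LAD.
- Reconcile Figure 3.2 with the two arms in 3.2.1.

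The cost is a change of text, a redrawn figure and a less favourable stated power. Recruitment and conduct are unaffected.
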